### Concealment Mechanism {16b}

The randomization procedure will be conducted by a biostatistician who then passes the assignment directly to the Study Director. The Study Director will notify community health workers of their church assignments. The data coordinating center (DCC) study liaison will be the only additional person notified of the randomization assignments.

### Implementation {16c}

At each screening event at the churches, two CHWs and at least one RA will be present, in addition to either the project coordinator or study director. The team will assist with conducting eligibility screenings, scoring screeners, and enrolling eligible participants into the study. Following the screenings, RAs will schedule a time to meet with the participant for the baseline within the next week after screening and consent.

## Assignment of interventions: blinding

### Procedure for blinding {17a}

All research assistants collecting data at all waves will be blinded.

### Procedure for unblinding if needed {17b}

There will be no circumstances in which unblinding will be necessary.

## Data Collection and management

### Plans for assessment and collection of outcomes {18a}

The primary outcome measure, an adapted version of the Behavioral Risk Factor Surveillance System (BRFSS) CRC screening tool, and the DIS will be collected at 6 months. The secondary outcome LS7 will be collected at 6 and 12 months. Table 1 outlines the measures used to construct the baseline, 3-month, 6-month, and 12-month assessments. Major timepoints in the study protocol are outlined in Table 2.

#### Identify contextual factors that act as facilitators or barriers of CRC screening update (secondary outcome)

We will employ a concurrent, convergent mixed-methods research design^52^ to gather multi-level factors that influence both delivery of the intervention and its impact on key health behaviors. We will build off of the CFIR.^17^ Data collection and analysis will be conducted concurrently (QUAN+QUAL)^52^ to understand effectiveness and implementation outcomes using a more nuanced, in-depth approach. First, after reaching the 6 month follow up point, we will use the CFIR as a guide to conduct semi-structured interviews or focus groups across each level of the Socio-Ecological Model: individual [randomly selected CRC screening guideline discordant subjects across the usual care and intervention groups (n=22 of each for total of 44)], interpersonal [CHWs (n=44)], institutional [clergy from each site (n=22)], and community [clinic providers (n=11)]. These interviews will enable a deeper understanding of the multi-level barriers and facilitators to behavior change and screening uptake across CFIR domains (policy, organizational/church, implementer, intervention, implementation processes) that impact delivery of the intervention; we will apply a recently adapted version of this framework that employs a race-conscious frame to CFIR constructs and domains to understand ways that structural racism interacts with intervention implementation and uptake.^16^ Additionally, to enhance understanding of the mechanisms through which the intervention works (e.g. how and why?), CHWs will complete brief surveys about their role commitment, self-efficacy, organizational, and role-related benefits/challenges, informed by our extensive former work on successful implementation of CHW programs in AA community settings and churches.^53, 54^ Each pastor will also complete the Faith-Based Organization Capacity Inventory (FBO-CI)^55^ interview to assess their church’s health promotion experience and research capacity, which allows us to explore whether there are differences in impact and implementation of the intervention based on these characteristics. Implementation data will be collected on key indicators from the RE-AIM evaluation framework from implementation science, including Reach – the absolute number of congregants willing to participate; Adoption - the percentage of churches that employ 12 CRC Screening identification events in a year; and Maintenance - the extent to which CRC screening referrals continue to be delivered 1-year following the end of the data collection period in the absence of research support.^56, 57^ This information will help identify significant challenges or inequities along the implementation continuum. All interviews are conducted by trained RAs either in person or over the telephone.

### Plans to promote participant retention and complete follow-up {11c}

#### Plan for church and participant retention

Each church will receive a $1,000 donation for their time and space. Pastors will sign an agreement that commits their church to: 1) identify a church champion to assist CHWs implement screening days; 2) host at least 12 CRC screening drives per year. We will also implement proven retention strategies for AA participants such as: regular telephone contact to remind participants of upcoming study appointments; toll-free study telephone number for contacting study staff; diverse study staff; and direct assistance with transportation to study visits. Participants will receive an incentive of $50 for completion of baseline, 6-month and 1-year measures and $25 for completing the 3-month FFQ.

#### Plan for CHW retention

We have a successful retention program for our CHWs that has led to an 85% retention of our CHWs cohort. The program includes recreational engagement and relationship building; continuous health education; and mindfulness training. CHWs will meet monthly to discuss challenges, and will have 24-hour access to PIs via cellphone.

### Data management {19}

This trial will partner with the DCC which will be responsible for the following: 1.) development of a computer-based data collection system, 2.) training staff and data collectors, 3.) randomization, 4.) monitoring data and quality control, 5.) data processing, and 6.) data analysis. Study milestones and progress will be monitored by the DCC. Study progression will be reported through regular reports.

All screening and assessment data will be collected using a REDCap form which will increase the accuracy of the data collected as responses will be limited to pre-provided values. Scoring and cleaning processes will be developed by the DCC for scales within instruments. This cleaning process will provide an additional layer of protection to double check the accuracy of the data. The DCC project manager will be responsible for periodically reviewing the data collected to ensure there are no duplicate records, incorrect collection dates or times, or out of range values. Following any corrections made, the project manager will review the items to ensure no anomalies remain. Quality assurance measures will include periodically reviewing entire files.

Data collection will be completed on secure laptops and office desktop computers that are password protected and encrypted. Laptops and hardcopies of data will be stored in a locked storage area on site.

Electronic data will be backed up daily or weekly to a backup server at the DCC. Additional backup hard drives will be securely stored in a fireproof safe. Protected Health Information (PHI) will be stored in a secure device that is not connected to the internet. All devices will be password protected and their drives will be encrypted. The network will be protected against hackers and unauthorized internet access though a hardware-based firewall device, which will also serve to filter out spam. Devices will be protected against malware using anti-virus software that is automatically updated through “push-technology.”

### Confidentiality {27}

#### Patient information

Participant confidentiality will be protected in multiple ways. Specifically, participant data collected following consent by participants will be protected. RAs will collect, gather, and enter required data onto study data forms. Screened participants who do not meet study eligibility will only have specific screening data entered into the study database. The collected data will include gender, age, race and reason for exclusion. When personal data e.g., telephone numbers, email address, and home addresses – are collected, they will be stored on password protected computers with secure servers and firewalls. The information will only be available to IRB approved study personnel who are required to take HIPAA and CITI training. Of note, all CHWs in this study will be required to take HIPAA and CITI training as part of their on-boarding process to participate in this study. PHI will be removed from the study database upon study completion. All data obtained from this study will be used for research purposes only and will comply with Federal HIPAA regulations. These data will be de-identified using a unique identifier whose code is only known to research staff and stored in a secure encrypted electronic database such as REDCAP.

#### Paper assessments and files

The Project Coordinators will prepare and maintain a participant-specific binder for each participant containing all case report form (CRF) records. A regulatory file will also be maintained to include the IRB-approved Protocol, original Informed Consent documents, HIPAA forms and other study-related regulatory documents. All paper research records and CRFs will be maintained in a locked file cabinet in a secure facility within the Department of Neurology. Access to the research records and study database will be restricted to study personnel as approved by the MPIs and IRB. As with all studies conducted at Columbia University, this study is also eligible for a random audit by Columbia University’s Office of Compliance.

#### Electronic assessments

This study will use Research Electronic Data Capture (REDCap) for data capture and management.

#### Secure data transfer procedures

Statisticians at the DCC will download data from assessments from the Columbia secure server through VPN connections.

#### Data access

Access to data will require two steps. First, the user must log into the University VPN after which they will be directed to log into the Columbia file server. Study personnel will reset their passwords every 6 months and be required to use password protected laptops/computers. The data will be kept on HIPAA compliant and encrypted servers that will only be accessible to IRB approved personnel.

Further efforts to ensure participant confidentiality will include the following:

Study data will be linked with a unique code number assigned to each study participantParticipant names, code numbers, and study data will be stored in a locked folder that can be accessed only by study staffInformation kept on the computer will be coded numericallyAll study data will be reported in a group format with no individual data presentedRecords will be made available only to research personnel, and Federal, State, and Institutional staff, who may review records as part of routine auditsConfidential subject records may be accessed by legal advocacy organizations with authority under State law, but this information cannot be re-disclosed without participant consent.

### Plans for collection, laboratory evaluation, and storage of biological specimens for genetic or molecular analysis in this trial/future use {33}

To assess Aim 3, blood will be obtained from participants through a finger stick test using a point of care device. No biological specimens will be stored for genetic or molecular analysis in this trial/future use. RAs will collect all finger stick measures in a private space within the church setting following all safety precautions.

## Statistical methods

### Statistical methods for primary and secondary outcomes {20a}

#### Power analysis for Aim 1

This aim compares the effect of the SBIRT to RAU on CRC screening uptake. It is hypothesized that the intervention will lead to increased CRC screening (colonoscopy or stool-based test - the primary outcome) compared to RAU at 6-months. An intent-to-treat (ITT) set of analyses is proposed, with the alpha level set at 0.05. The sample size is based on the number of subjects needed to provide adequate power to detect the hypothesized group differences in the primary outcome, adjusted for clustering within churches. The comparisons of SBIRT to RAU on the guideline-concordant CRC screening rate will be conducted using a logistic regression model:

$\text{logit}(p)=\text{log}\left(\frac{p}{1-p}\right)=\beta_{0}+\beta_{1}X+\tau_{c}$ where X is a binary variable (0 for usual care and 1 for SBIRT intervention), *τ*_*c*_ is a random effect for clustering within churches, and p = prob(Y=1, CRC screening rate). The hypothesis H_0_: *β*_1_ = 0 vs H_1_: *β*_1_ = *β** will be tested with the formula for determining the total sample size.^58–61^: $n^{*}=\frac{{\left(V{\left(0\right)}^{1/2}Z_{1-\alpha /2}+V{\left(\beta^{*}\right)}^{1/2}Z_{1-\beta }\right)}^{2}}{P_{1}\beta^{*2}}\left(1+2P_{1}\delta \right)$ with $\beta^{*}=\text{log}\frac{P_{2}\left(1-P_{1}\right)}{P_{1}\left(1-P_{2}\right)}$, with $V(0)=\frac{1}{1-B}+\frac{1}{B}$, $V\left(\beta^{*}\right)=\frac{1}{1+B}+\frac{1}{\text{Bexp}\left(B^{*}\right)}$, *δ* = (*V*(0)^1/2^ + *V*(*β**)^1/2^*R*)/(*V*(0)^1/2^ + *V*(*β**)^1/2^), *R* = *v*(*β**)*B*(1 − *B*) exp(2*β**)/(*Bexp*(*β**) + (1 − *B*))^2^, where *P*_1_, *P*_2_ are the CRC screening rates of usual care and SBIRT (intervention), respectively, and B is the proportion of the sample assigned to each of two arms (B=0.5), *δ* is a small rate adjustment, when *P*_1_ < 0.2 (*δ* = 0 when *P*_1_ ≥ 0.20), adjusting for unreliability and clustering (g=1+(s-1)*icc):*n* = *n***g*/*R*_*el*_. The assumptions are: for α=0.05 (2 tailed test), 1-β=0.80 (power), *R*_*el*_ = 0.95 (adjusted for unreliability), g=1.57 (variance inflation factor adjusting for clustering), with cluster size s=20 and icc (intracluster correlation coefficient=0.03). *P*_1_ (X=0, usual care group), *P*_2_ (X=1, intervention group), B=0.5, n=total sample size, and power for n=396 (m=198 per group, about 11 churches per group with attrition rate=10% at 6 months with an average of 20 participants per church)/

Regarding the CRC screening rate, a sample size of 198 subjects per group (10 to 12 churches per group, average of 20 subjects per church, attrition rate of 10% at 6 months) is required to provide 80% or greater power to detect a group difference of 15% (a clinically meaningful increase) in the rates of completed colorectal cancer screening at 6 months. Thus, power will be sufficient to detect the hypothesized difference from baseline in both arms. As shown above, these calculations assume a baseline rate of 0 and scenarios with increase in screening rates in the usual care group from 0.20 to 0.50. Thus, with an overall sample size of 440 subjects or 220 per arm (11 churches per arm with 20 subjects in each church), the study is powered adequately, even with attrition. Based on our prior study in which approximately 50% of AAs above age 50 years were not up to date with screening,^48^ we will screen at least 40 adult churchgoers aged 45 years and older per church for study eligibility (total screening = 880 subjects).

#### Power analysis for Aims 2 and 3

Aim 2 is to evaluate the effect of a CAP incorporated into the intervention arm on DIS at baseline and 6-month follow up; and Aim 3 is to evaluate the effect of CAP on changes in LS7 at baseline, 6-months and 12 months. Sensitivity analyses will be performed including data from the 3-month wave. Power calculations were performed for an analysis of covariance (ANCOVA)-type model: *y*_*ijk*_ = *μ*_*jk*_ + *y*_*i*0_ + *τ*_*c*_ + *e*_*ijk*_, where *μ*_*jk*_ is the group mean for follow up DIS and LS7, *y*_*i*0_ is the baseline measure, j=1,2 follow-ups and k=0, 1 for group, *τ*_*c*_ is a random effect for clustering within church. The power analysis equation for one follow-up is: $n=\frac{2{\left(z_{\alpha }+z_{\beta }\right)}^{2}\sigma^{2}\left(1-\rho^{2}\right)g}{d^{2}R_{el}}$: where *ρ* is the correlation between the outcome and baseline values, *σ* is the standard deviation, *d*_*I*_ is the follow-up difference between 2 groups, *R*_*el*_ is the reliability of the outcome, adjusting for clustering within churches, g=1+(s-1)*icc, and n is number of subjects per group.

The power analysis equation for 2 follow ups examined in aim 3 is: $m=2g{\left(z_{\alpha }+z_{\beta }\right)}^{2}\sigma (1-\left.r_{c}^{2}\right)\sum \sum r_{ij}/{\left(R_{el}\sum d_{i}\right)}^{2}$, and $r_{c}=\sum r_{i1}/\sqrt{\sum \sum r_{ij}}$, where g is the clustering adjustment for church, *r*_*ij*_ is the correlation matrix for 2 follow-ups, *r*_*i*1_ is the correlation between baseline and 2 follow-ups and di is the follow-up difference between 2 groups for two follow-ups, with i=1,2 and j=1,2. The correlation between the baseline and 2 follow ups (half year, 1 year) will be modeled as CS (compound symmetry (constant: *r*_*i*1_ = *ρ*, *ρ*)) and AR_1_ (Autoregressive (Exponential decay, $r_{i1}=\sqrt{\rho },\rho$)). The difference between the 2 follow-ups will be modeled as unequal: *d*_*i*_=(¾d, d) -- the half year follow-up difference between 2 groups is ¾ of the 1 year study-end difference; and equal: *d*_*i*_=(d, d) -- the two follow up group differences are the same. The minimal detectible effect size (expressed as Cohen’s d) with m subjects per group was calculated assuming: α=0.05 (two-tailed), *R*_*e*_(reliability), g=1.57 (clustering adjustment for church as descripted above), m=198 per group at 6 month follow up assuming at least 2 waves of data and an intent-to-treat (ITT) model for the third wave (220 subjects at baseline, 10% attrition at 6-month follow-up). The correlation between baseline and 1 year follow up is assumed to be 0.5, 0.6 and power=80%. Two scenarios regarding the covariance structure and the difference between groups were also examined.

Dietary inflammation score (DIS): For the DIS outcome, with baseline and one follow up, it is assumed that σ=1 for the standardized score. Assuming α = 0.05 for a two-tailed test, 10% attrition, with m= 198 per group at 6 months (220 at baseline, 11 churches per group), adjusting for reliability=0.8 and the clustering effect of church, it will be possible to detect a small effect size of δ=0.303 (Cohen’s d=0.303), with power of 0.80. With the correlation between baseline and follow up equal to 0.6, the Cohen’s d=0.280 (an effect size of δ=0.280).

For the LS7 outcome, with baseline and two follow ups, it is assumed that σ=2.7 (standard deviation). Assuming the difference between the 2 groups is unequal will result in lower power than if equal. A correlation structure of compound symmetry will result in lower power than autoregressive (AR). The primary analyses assume ITT for the 3rd wave, α = 0.05 for a two-tailed test. However, effects assuming 20% attrition, with m = 176 per group at 1 year study-end were also calculated (baseline m=220, 6-month m=198 and 1 year m=176). With an m = 198 per group at 6-months (ITT model for 3rd wave), it will be possible to detect an effect size of δ=0.764 (Cohen’s d=0.283), with power of 0.80. With the correlation between baseline and follow up equal to 0.6, the Cohen’s d=0.265 (which translates to an effect size of δ=0.716). Examining different scenarios regarding the difference between the groups and the correlation structure of compound symmetry, or AR, the detectable effect sizes range from δ=0.645 (Cohen’s d=0.239) to δ=0.810 (Cohen’s d=0.300) with power of 0.80.

#### Analysis for Aim 1

Logistic-type regression analyses will be used to test the hypothesis that those assigned to SBIRT will have significantly higher CRC screening rates compared to those randomized to RAU at 6 months. Clustered sampling effects due to churches will be incorporated using a multilevel modeling approach. Ideally, the randomization of participants to treatment arm and the absence of significant selection and/or attrition biases will obviate the need for inclusion of covariates. In the event that the logit analyses indicate one or more sources of potential bias, the predicted values of those analyses will be included as covariates in a multilevel logistic regression model (SAS, PROC GLIMMIX).

#### Analysis for Aims 2 and 3

An ANCOVA-type model, using SAS Proc Mixed will be used to allow for flexible modeling of assumptions, treatment of missing data and inclusion of all subjects with at least one wave of data. The basic model is: *Y*_*i*_ = *β*_0_ + *β*_1_*Y*_0*i*_ + *βX*_*i*_ + *e*_*i*_. Based on prior analytic experience with the outcome variables, it is not expected that transformations will be necessary; however, distributions will be examined for confirmation. The continuous longitudinal outcomes will be modeled as functions of baseline values, randomization groups, covariates and interactions as necessary. Prior to analyses, baseline values of all variables will be examined. Variables differing between the groups will be examined in secondary analyses.

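### The 80% power claimed for the primary outcome is not delivered: on the plan's own inputs, power for a 15-point difference is about 64–74% at usual-care rates of 0.20–0.50

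*Protocol article*

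**What the plan says.** All of this stands in the protocol article, Statistical methods {20a}, Power analysis for Aim 1.

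- **Claim:** 198 per group "is required to provide 80% or greater power to detect a group difference of 15% (a clinically meaningful increase"). The section concludes that the planned enrolment is adequate even after attrition.
- **Usual-care rates:** "scenarios with increase in screening rates in the usual care group from 0.20 to 0.50".
- **Error rates:** "for α=0.05 (2 tailed test), 1-β=0.80 (power").
- **Clustering:** "g=1.57 (variance inflation factor adjusting for clustering), with cluster size s=20 and icc (intracluster correlation coefficient=0.03"). A reliability divisor of 0.95 is also applied.
- **Numbers:** "m=198 per group, about 11 churches per group with attrition rate=10% at 6 months with an average of 20 participants per church", from 440 enrolled (220 per arm).
- **Formula:** a logistic-regression sample size with multiplier (1 + 2·P1·δ), where δ "is a small rate adjustment" that applies when P1 is below 0.20 and is set to zero from 0.20 upwards. The result is multiplied by g and divided by the reliability.

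**The concern.** The multiplier (1 + 2·P1·δ) grows with P1, yet the plan removes it from P1 = 0.20 upwards, which is the whole range of usual-care rates it considers. Without it, the required sample falls steadily as the usual-care rate approaches 0.50, although binomial variance is largest there. That suggests a formula used outside the range where it is valid.

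This is the power statement for the primary outcome. If power is overstated, a non-significant result would too readily be read as evidence that the intervention does not work.

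**Working it through.** **Inputs** (all from Power analysis for Aim 1): two-sided α = 0.05 (z = 1.960); power 0.80 (z = 0.842); P2 = P1 + 0.15; P1 from 0.20 to 0.50; 198 analysed per arm (396 in total); g = 1 + 19 × 0.03 = 1.57; reliability 0.95; B = 0.5. The 15% is read as an absolute difference.

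**Step 1. Reproduce the plan's figure.** With δ = 0, and 1/(1−B) in V(β*):

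n = [√V(0)·1.960 + √V(β*)·0.842]² / (P1·β*²) × 1.57/0.95

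At P1 = 0.20:
- β* = ln[(0.35 × 0.80)/(0.20 × 0.65)] = 0.767
- V(0) = 2 + 2 = 4
- V(β*) = 2 + 1/(0.5 × 2.154) = 2.929
- n* = (3.920 + 1.440)²/(0.20 × 0.589) = 244
- n = 244 × 1.57/0.95 = 403

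At P1 = 0.25 the result is 398. The stated 396 is therefore essentially what this formula gives. V(β*) is printed with 1/(1+B), but taken literally that gives 349 at P1 = 0.20. The slip is in the printed expression and evidently did not produce the 396.

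**Step 2. Why the formula fails here.** With δ = 0 its null variance for the log odds ratio is V(0)/(n·P1) = 4/(n·P1). For a binary outcome with rate P1 in two equal arms it is 4/[n·P1(1−P1)]. The missing factor 1/(1−P1) is 1.25 at P1 = 0.20 and 2.00 at P1 = 0.50, so the approximation suits rare outcomes only. The plan's own δ, if computed, is about 1.17 at P1 = 0.20 and 1.14 at 0.50. The omitted multiplier is then 1 + 2 × 0.20 × 1.17 = 1.47, and 1 + 2 × 0.50 × 1.14 = 2.14.

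**Step 3. Standard calculation on the same inputs.** Effective n per arm = 198 × 0.95/1.57 = 119.8. With p̄ the mean of P1 and P2:

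power = Φ{[0.15·√119.8 − 1.960·√(2p̄(1−p̄))] / √(P1(1−P1) + P2(1−P2))}

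At P1 = 0.20: (1.642 − 1.238)/0.622 = 0.649, and Φ(0.649) = 74.2%.

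The n needed per arm before inflation is [1.960·√(2p̄(1−p̄)) + 0.842·√(P1(1−P1) + P2(1−P2))]²/0.15². At P1 = 0.20 this is (1.238 + 0.524)²/0.0225 = 137.9. The analysed total is 2 × 137.9 × 1.57/0.95 = 456.

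| P1 vs P2 | Plan formula, δ = 0: total | Plan formula, δ kept: total | Standard: n per arm before inflation | Standard: total | Power at 396 | Difference detectable at 80% |
|---|---|---|---|---|---|---|
| 0.20 vs 0.35 | 403 | 592 | 137.9 | 456 | 74.2% | 16.2 points |
| 0.30 vs 0.45 | 383 | 646 | 162.3 | 537 | 67.1% | 17.6 points |
| 0.40 vs 0.55 | 328 | 626 | 172.8 | 571 | 64.4% | 18.0 points |
| 0.50 vs 0.65 | 251 | 538 | 169.3 | 560 | 65.3% | 17.7 points |

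**Step 4. Sensitivity over P1 = 0.20–0.50.**

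| Variant | Power |
|---|---|
| Wald test on the risk difference | 65–75% |
| Wald test on the log odds ratio | 64–73% |
| t reference, 20 df (22 churches) | 61–71% |
| No reliability divisor | 67–76% |
| g = 1.51 (18 analysed per church), reliability kept | 66–76% |
| g = 1.51, no reliability divisor | 68–78% |
| All 440 analysed, g and reliability kept | 69–79% |
| All 440 analysed, no reliability divisor | 71–81% (above 80% only at P1 = 0.20) |

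A beta-binomial simulation (11 churches of 18 per arm, ICC 0.03, no reliability loss, 40,000 runs) gave 74.8%, 67.1%, 64.1% and 65.4% at P1 = 0.20, 0.30, 0.40 and 0.50 with a cluster-level t test. A z test that takes the design effect as known gave 78.5%, 71.0%, 69.3% and 69.7%.

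**The case against.** The best defence is that the plan applied its cited method correctly. The total of 396 follows from the printed formula to within 2% at P1 = 0.20–0.25, and at 396 that formula reports 79–95% power over the range. On this view the lower figures come from changing the method. The first half stands: this is not a slip of calculation. The second half does not rescue the claim. Power is a property of the design, and a formula whose required sample falls from 403 to 251 as the outcome variance rises does not describe it. The plan's own formula with δ retained also contradicts 396, since it asks for 538–646.

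Several narrower points are fair:

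- Restoring δ is not a cure. It overshoots the standard answer at P1 = 0.20–0.40 (592 vs 456, 646 vs 537, 626 vs 571) and falls below it at 0.50 (538 vs 560).
- The 1/(1+B) misprint did not drive the stated number.
- The risk of a missed effect is about one in four at P1 = 0.20 and nearer one in three from about 0.30 upwards.
- The simulations use cluster-level tests rather than the planned multilevel logistic model, and matching churches on size is not credited.
- The section refers to scenarios shown above, but no such table is visible, so its rows could not be checked one by one.
- Using 18 per church and dropping the reliability divisor narrows the gap, but power still stops at 78%.

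**Conclusion.** The concern holds. With 198 analysed per arm, g = 1.57, reliability 0.95 and a two-sided 5% test, power for an absolute difference of 15 points is 74% at a usual-care rate of 0.20. It falls to 64% at 0.40–0.45 and is 65% at 0.50, so it does not reach 80% at any rate in the stated range. The type II error is 26–36%. Reaching 80% would take 456–571 analysed, against 396. Equivalently, the design detects about 16–18 points with 80% power.

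This rests on the plan's own ICC, cluster size, attrition and reliability, and on a normal reference; allowing for only 22 churches lowers power to 61–71%. If 15% were meant as a relative increase, the absolute difference would be smaller and power lower still. The estimator, the test and the type I error are not affected.

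**What to change.** In Power analysis for Aim 1:

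1. Drop the formula with the δ = 0 rule. Replace it with a standard clustered two-proportion calculation, or with a simulation of the planned multilevel logistic model that reflects 20 degrees of freedom for 22 churches.
2. Restate the claim, for example:

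> With 198 participants analysed per arm (ICC 0.03, design effect 1.57, reliability 0.95, two-sided α = 0.05), power to detect a 15-percentage-point difference is about 64–74% for usual-care rates of 0.20 to 0.50. Power of 80% is reached for a difference of about 16–18 percentage points.

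3. Amend the sentence that calls the study adequately powered even with attrition so that it agrees.
4. If the formula is kept anywhere, correct V(β*) to 1/(1−B).

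The cost is protocol and SAP wording only, and the stated power becomes less favourable. No change in enrolment is asked for. Recruitment is expected to run to 2027, so the statement can be corrected before results are known.

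### The DIS detectable effects are declared two-tailed but computed with the one-sided 5% quantile (about 70% power, not 80%); the LS7 figures show the same pattern if reliability is 0.8

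*Protocol article*

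**What the plan says.** The subsection on power for Aims 2 and 3 (Protocol article, Statistical methods for primary and secondary outcomes {20a}) gives detectable effects at 80% power.

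- **Test level.** For DIS: "Assuming α = 0.05 for a two-tailed test, 10% attrition, with m= 198 per group at 6 months". For LS7: "The primary analyses assume ITT for the 3rd wave, α = 0.05 for a two-tailed test".
- **DIS.** The headline is "it will be possible to detect a small effect size of δ=0.303 (Cohen’s d=0.303), with power of 0.80", followed by 0.280 at a correlation of 0.6.
- **LS7.** The headline is "it will be possible to detect an effect size of δ=0.764 (Cohen’s d=0.283), with power of 0.80", followed by d = 0.265 (0.716 points) at a correlation of 0.6. Across scenarios, "the detectable effect sizes range from δ=0.645 (Cohen’s d=0.239) to δ=0.810 (Cohen’s d=0.300) with power of 0.80".

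The sample size formulas for these two aims are printed with z_α. The Aim 1 formula in the same section is printed with Z_{1−α/2}.

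**The concern.** A two-tailed 5% test uses the critical value 1.96. If 1.645 was used instead, every detectable effect is too small by the factor (1.645 + 0.842)/(1.960 + 0.842) = 0.888, and the power claimed for the stated effects is too high. Aims 2 and 3 each carry a hypothesis about a group difference. A reader judging whether the trial can answer them relies on these figures, because the plan gives no other account of its sensitivity for DIS and LS7.

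**Working it through.** **DIS: inputs, all from the power subsection of {20a}.** Two-tailed alpha 0.05; power 0.80 (z_β = 0.8416); m = 198 per group; g = 1.57; reliability R = 0.8; σ = 1; ρ = 0.5 or 0.6, where ρ "is the correlation between the outcome and baseline values". The 0.303 is taken to belong to ρ = 0.5, because the next sentence attaches 0.280 to 0.6.

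The one-follow-up formula, solved for the effect, is d = √[2(z_α + z_β)²(1 − ρ²)g / (mR)], with mR = 198 × 0.8 = 158.4.

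Reproducing the plan's figures with z_α = 1.645, so that (z_α + z_β)² = 6.183:

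- ρ = 0.5: √(2 × 6.183 × 0.75 × 1.57 / 158.4) = 0.3032 (stated 0.303)
- ρ = 0.6: √(2 × 6.183 × 0.64 × 1.57 / 158.4) = 0.2801 (stated 0.280)

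With the declared two-tailed z = 1.960, so that the square is 7.849:

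- ρ = 0.5: 0.3416
- ρ = 0.6: 0.3156

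The ratio is 2.8016/2.4865 = 1.127. Two-sided power at the stated effects is Φ(2.4865 − 1.960) = Φ(0.5265) ≈ 0.70. Reaching 80% at d = 0.303 would need 2 × 7.849 × 0.75 × 1.57 / (0.303² × 0.8) ≈ 252 per group, against 198.

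**LS7: inputs.** σ = 2.7; g = 1.57; m = 198, or 176 with 20% attrition; ρ = 0.5 or 0.6; compound symmetry (CS) or autoregressive (AR) correlation; follow-up differences (¾d, d) or (d, d). **No reliability value is printed for LS7; 0.8 is assumed here.** For AR, the correlation between the two follow-ups is taken as √ρ, the same half-year step as the printed baseline correlations.

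The two-follow-up formula, taken with σ² and with R to the first power, gives d = √[2g(z_α + z_β)² S / (mR)] / D. Here S = ΣΣr_ij − (Σr_i1)², and D = 1.75 (unequal) or 2 (equal). S is 3 − 1 = 2 for CS at 0.5, 3.2 − 1.44 = 1.76 for CS at 0.6, and 3.549 − 1.890 = 1.660 for AR at 0.6.

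| Stated d | Scenario | z = 1.645 | z = 1.960 | Points at 1.960 (× 2.7) |
|---|---|---|---|---|
| 0.283 | CS, unequal, ρ 0.5, m 198 | 0.2829 | 0.3188 | 0.861 |
| 0.265 | CS, unequal, ρ 0.6, m 198 | 0.2654 | 0.2990 | 0.807 |
| 0.300 | CS, unequal, ρ 0.5, m 176 | 0.3001 | 0.3381 | 0.913 |
| 0.239 | AR, equal, ρ 0.6, m 176 | 0.2392 | 0.2695 | 0.728 |

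The last two rows are the largest and smallest of the eight scenarios at m = 176, which fits the stated range.

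**LS7: sensitivity to the assumed reliability.** Two-sided power at the stated d = 0.283 is:

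| R | 0.80 | 0.85 | 0.90 | 0.95 | 1.00 |
|---|---|---|---|---|---|
| Power | 70.1% | 72.7% | 75.1% | 77.4% | 79.4% |

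For 0.283 to be a two-sided 80% value, mR would have to be 2 × 1.57 × 7.849 × 2 / (1.75 × 0.283)² ≈ 201. That means R ≈ 1.015, which is not possible.

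**The case against.** The strongest defence concerns LS7. Its reliability is not stated: 0.8 is printed for DIS, and the only other printed value is 0.95, for Aim 1. The match also requires repairing the printed two-follow-up formula, supplying one AR correlation and assigning both ends of the range to m = 176. A reader might infer that every figure for both outcomes is proven to carry 70% power and that 0.319 and 0.299 are the correct LS7 values. The documents do not support that much. For LS7 the 70% and the replacement values are conditional on R = 0.8. What survives without fixing R is that, in these scenarios, no reliability up to 1 brings the stated LS7 effects to 80% two-sided.

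A rival explanation is a two-sided calculation with the reliability adjustment left out. It gives 0.3055 and 0.2822 for DIS and 0.2851, 0.2675, 0.3024 and 0.2410 for LS7. These are close, but all six miss in the third decimal, and for DIS the text says that reliability 0.8 was applied.

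It is also fair to say that z_α can be shorthand for the two-sided critical value, so the notation alone proves nothing; the numbers carry the point. The σ and R_el misprints change no stated figure.

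Finally, a reader might infer that the trial's size is wrong. It is not affected: the 22 churches and 440 participants rest on the primary outcome, whose formula uses Z_{1−α/2}.

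**Conclusion.** The point holds firmly for DIS. From the stated inputs, the detectable effects are 0.342 and 0.316 rather than 0.303 and 0.280, and two-sided power at the stated effects is about 70%. The one inference is that 0.303 belongs to ρ = 0.5.

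For LS7 the same error is by far the likeliest explanation, since one quantile and one reliability reproduce all four figures, but it rests on the assumed reliability of 0.8. Under that assumption the two-sided values are 0.319 and 0.299 (0.861 and 0.807 points), the range is 0.270 to 0.338 (0.728 to 0.913 points), and power at the stated effects is about 70%. Over R = 0.8 to 1.0 that power runs from about 70% to 79%, so it stays below 80%.

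Normal quantiles are used throughout, as in the plan. This is a moderate correction to stated figures for secondary outcomes. The planned analysis, the two-tailed level and the Aim 1 sample size do not change.

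**What to change.** - Recompute the detectable effects for both outcomes with z_{1−α/2} = 1.96.
- Restate DIS as d = 0.342 (ρ = 0.5) and 0.316 (ρ = 0.6), or keep the present effects and report about 70% power.
- State the reliability used for LS7 and restate its effects to match. If it is 0.8, they are 0.319 and 0.299 (0.861 and 0.807 points), range 0.270 to 0.338 (0.728 to 0.913 points).
- Print z_{1−α/2} in both formulas. In the two-follow-up formula, print σ² and take R_el out of the square.

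The cost is a change of wording and figures, with no change to design, sample size or analysis. The stated sensitivity for Aims 2 and 3 becomes less favourable: detectable effects are 12.7% larger for DIS, and for LS7 if its reliability is 0.8.
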